## Research aims and hypothesis

2

In this study, we aim to (1) assess the longitudinal relationship between mushroom consumption and cognitive decline, measured by the absolute change in Mini Mental State Examination (MMSE) scores over a median of 10 years among surviving DaHA participants; (2) test the effects of mushroom powder (two 500 mg capsules per day) on cognitive function measured using the Symbol Digit Modality test (SDMT), the Color Trail Test (CTT) and the Rey Auditory Verbal Learning Test (RAVLT) over 12 months and 24 months, in comparison with controls who consume placebo; (3) examine the underlying protective mechanisms using biomarkers of aging (epigenetic clocks and inflammation) and measuring blood ergothioneine levels; (4) explore epigenome-wide DNA methylation changes following mushroom powder intervention and assess whether such changes correlate with cognitive and biomarker outcomes, without presupposing a beneficial direction. We hypothesized that (1) mushroom consumption will predict slower cognitive decline in a dose-dependent manner over a median 10-year period among DaHA participants; (2) daily mushroom powder consumption over 12 and 24 months will improve cognitive function (processing speed, executive function, memory) among middle-aged and young-old adults; (3) daily mushroom powder consumption will lead to favorable changes in inflammatory marker of aging that correlate with the increase in bioactive compounds from mushrooms; (4) daily mushroom powder consumption will lead to changes in DNA methylation profiles.

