### Randomization

3.3

Trial participants will be randomly assigned to one of the two arms in an equal ratio using a web-based randomization system. Randomization will be performed by the Singapore Clinical Research Institute (SCRI) on a pay-for-service arrangement. The randomization sequence will be concealed from the investigators, ensuring allocation concealment.

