To examine the underlying protective mechanisms: The levels of biomarkers will be treated as continuous variables. Changes in biomarkers will be calculated by comparing post-intervention levels to pre-intervention levels from intervention and control and represented in percentage (%). These changes will then be compared between the intervention and control groups. Furthermore, paired two-tailed t-tests will be performed to assess whether biomarker levels differ between pre-intervention and post-intervention measurements within each group (control and intervention). To analyze the ergothioneine data, we will use a “change-versus-change’ approach, using repeated ergothioneine measurements as predictors to examine their relationship with changes in cognition and other biomarkers. We will further employ Structural Equation Modeling (SEM) to assess how the intervention affects cognitive function, with ergothioneine as a hypothesized mediating factor. In the SEM, we will adjust for age, sex, education (social class proxy), BMI, APOE ε4 status, baseline supplement use (curcumin, Ginkgo, omega-3), individual metabolic variations by including plasma liver enzymes (ALT, AST) and baseline renal function & ergothioneine levels as covariates, and compliance rate. Interaction terms will test effect modification.

To examine the epigenetic changes associated with ET-Rich mushroom consumption: Analysis of epigenome-wide methylation data will be performed using a modified version of the CPACOR pipeline(Lehne et al., 2015). Briefly, we will normalize marker intensities by quantile normalization. Single-marker tests using logistic regression will be used to examine the association of mushroom consumption with each autosomal CpG site (yes/no), adjusted for age and sex. Principal components from intensity values of Infinium control probes will also be included as covariates in the regression models. Finally, the association results will be adjusted for the genomic control inflation factor. We will subsequently develop a methylation risk score (MRS) model by taking a weighted approach (by effect size) for the CpG loci identified to be associated with mushroom consumption. Figure 3 describes the flow of study participants.

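### Genomic control is applied unconditionally to the methylation tests, with no unadjusted or global analysis beside it, so a broad effect of the powder could be scaled away unseen

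*Protocol article*

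**What the plan says.** In the protocol article, section 2 (Research aims and hypothesis) gives the fourth aim as to "explore epigenome-wide DNA methylation changes following mushroom powder intervention", with no direction presupposed. The matching hypothesis is that "daily mushroom powder consumption will lead to changes in DNA methylation profiles". It does not say how many sites are expected to change.

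Section 3.5 (Methods of analysis) describes the testing, with sex as the second adjustment variable: "Single-marker tests using logistic regression will be used to examine the association of mushroom consumption with each autosomal CpG site (yes/no), adjusted for age and". It adds: "Principal components from intensity values of Infinium control probes will also be included as covariates in the regression models". The last step is: "Finally, the association results will be adjusted for the genomic control inflation factor". A methylation risk score, weighted by effect size, is then built "for the CpG loci identified to be associated with mushroom consumption".

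Section 3.3 (Randomization) fixes the design of the comparison: "Trial participants will be randomly assigned to one of the two arms in an equal ratio using a web-based randomization system".

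No value of lambda is named above which the correction applies. No unadjusted result, permutation reference or global test of a methylation shift is described.

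**The concern.** Genomic control divides every site's chi-square by lambda, the observed median chi-square over its theoretical null median. The median site therefore has p = 0.50 after adjustment, whatever the treatment does. This is a sound safeguard when excess in the typical statistic is artefact, as it often is in observational work.

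Here arm is randomised and technical variation is already modelled through the control-probe components, so a further source of excess has to be considered: a real effect of arm at many sites. The adjustment cannot tell this apart from artefact or chance. The broader the true response, the larger lambda becomes and the more significance every site loses.

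Two things are at stake. A broad response could leave few or no significant sites and be read as no support for hypothesis 4. The risk score, which uses only the loci that pass, could lose many of them. As nothing is planned beside the adjusted results, a reader could not distinguish a true null from a broad response that had been scaled away.

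**Working it through.** **The plan's own figure.** The article gives no lambda, methylation effect size or site-level threshold. Its only computable figure here is the sample size. With d = 0.30, two-sided alpha 0.05 and 90% power, 2 × (1.960 + 1.282)² / 0.30² = 233.5, so 234 per arm; the t-based figure is 234.5, so 235, as stated. Allowing 20% attrition, 235 / 0.8 = 294, against 300 planned. The number left at 24 months is 300 × 0.8 = 240 per arm.

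**Assumptions, not in the article.** 240 per arm analysed; 850,000 sites (the article says over 850,000); Bonferroni threshold 0.05 / 850,000 = 5.9 × 10⁻⁸, so |z| > 5.42; and a two-group mean comparison standing in for the logistic test.

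**Power at one site.** For a standardised arm difference d, the expected z is d × √(240/2). At d = 0.6 this is 6.57. With genomic control, power = P(Z > 5.42 × √lambda − 6.57).

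- Unadjusted (lambda 1): P(Z > −1.15) = 87.5%.
- Lambda 1.30: 5.42 × √1.30 = 6.18; P(Z > −0.39) = 65%.
- Lambda 1.51: 5.42 × √1.51 = 6.66; P(Z > 0.09) = about 47%.

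The loss depends on the site effect. At lambda 1.31, power goes from 52% to 23% at 0.5 SD, from 98.8% to 92.8% at 0.7 SD, and falls by under 1 point at 0.8 SD.

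**How broad a response produces such a lambda.** Let a share π of sites have true effects drawn from N(0, 0.20²). Their chi-squares are then scaled by 1 + 120 × 0.04 = 5.8. Solve (1 − π)F(x) + πF(x/5.8) = 0.5, where F is the chi-square distribution function on 1 df; lambda = x / 0.4549.

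| Share of sites responding | Lambda | Power at the 0.6-SD site | Loss (points) |
|---|---|---|---|
| 1% | 1.01 | 86.8% | 0.7 |
| 5% | 1.07 | 83.3% | 4 |
| 10% | 1.14 | 78.0% | 10 |
| 20% | 1.32 | about 63% | 24 |
| 30% | 1.54 | 43.6% | 44 |

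With a fixed shift of 0.2 SD at the responding sites, the losses are larger: power is 86.3% at 1% of sites, 80.5% at 5%, 70.3% at 10% and 11.3% at 30%. In the extreme case where every site shifts by 0.2 SD, lambda is 10.6 and the median site's p-value moves from 0.028 to 0.50.

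**Behaviour with no effect.** Simulated null trials had 20,000 correlated sites, with five shared factors explaining 10 to 30% of the variance. At nominal 0.001, the unadjusted test rejected 0.0010 to 0.0011 of sites on average and the adjusted test 0.0007 to 0.0010. At 30% shared variance the 95% range of lambda was about 0.76 to 1.52; other runs of such a simulation put the upper limit between about 1.4 and 1.6. A single trial's lambda in that range does not by itself separate chance from a moderate broad effect.

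**The case against.** The strongest case for the plan has five parts.

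- **Breadth.** Neither the hypothesis nor the aim predicts a change at the typical site, and a score built from identified loci suggests a locus-level search. If about 1% of sites or fewer respond, the adjustment costs almost nothing. This stands. A reader might infer that hypothesis 4 requires a broad response which the plan is bound to suppress; the article does not say so.
- **Protection.** The nominal error rate of the unadjusted test is an average over trials. At 30% shared variance, lambda exceeded 1.3 in about 12% of simulated null trials, and in those the unadjusted test rejected about 0.0035 of sites at nominal 0.001, against about 0.0003 after adjustment. This stands too. It is why the tempting conclusion, that genomic control is wrong here and should be dropped, does not follow.
- **What is rescaled.** Genomic control rescales the null variance. It does not shift effect estimates or change the ranking of sites, so the score's weights are untouched. Only which loci pass the threshold is affected.
- **Exposure.** The tested variable is described as mushroom consumption, yes or no, and not as arm, and methylation data also exist for the DaHA cohort. In observational data the randomisation argument fails and the correction is an ordinary safeguard. Reading the variable as arm is reasonable, since the aim refers to the powder intervention, but the point is limited to that analysis. Even there, balance by design belongs to everyone randomised and is not guaranteed among those who complete 24 months.
- **Proportion.** The aim is exploratory, the error is lost power and not false positives, and an unseen analysis plan may hold diagnostics. This lowers the weight of the point. It does not alter the fact that the article fixes the adjustment without a condition.

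**Conclusion.** The point holds in a limited form. As written, the plan treats all inflation in the trial's methylation tests as artefact, and it describes nothing that would reveal a broad response if there were one. If lambda reached 1.3 to 1.5 because of a true effect, power at a 0.6-SD site would fall from 87.5% to about 65% and then 47%. The loss is about 4 to 10 points if 5 to 10% of sites respond (random effects, SD 0.20) and about 1 point or less at 1%, and it is smaller for larger site effects. These figures rest on 240 per arm, 850,000 sites, a Bonferroni threshold and an assumed breadth that the article does not give. The error is conservative and falls on an exploratory aim; the primary endpoint is not touched. It is worth correcting because the correction is cheap.

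**What to change.** For the trial's methylation analysis by arm only, keep the control-probe components and replace the genomic control sentence with text such as:

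*Per-site p-values for arm will be reported both without and with adjustment for the genomic control inflation factor, under Bonferroni or false discovery rate control. The observed inflation factor will be compared with its distribution under re-randomisation of the arm labels, and this comparison will be reported as the global test of hypothesis 4.*

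The plan should also say which of the two site lists feeds the methylation risk score.

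No new data are needed. The cost is computing time for the permutations and two lists to interpret. The unadjusted list can be inflated in a trial where lambda is high by chance; the permutation reference and the adjusted list guard against reading too much into it. Any analysis of cohort methylation data can keep the correction as planned.

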### Observational study

3.1

We will conduct a 10-year follow-up on all survivors from DaHA study. The proposed follow-up will consist of a cognitive assessment session using the MMSE and the Clinical Dementia Rating (CDR) scale. Cognitive decline will be quantified as the absolute difference between baseline and 10-year follow-up MMSE total scores. The average decline rate will be calculated by dividing the change in MMSE total score by the time elapsed between baseline and follow-up in years. Cognitive impairment will be defined by a CDR score of 0.5 or above. We have published widely on aging related topics using data from the DaHA cohort (Feng et al., 2019; Ye et al., 2023; Li et al., 2019; Liu et al., 2021). As DNA methylation and inflammation markers have already been measured in over 600 samples from DaHA participants, further bio-sampling is not required. Details of the cohort can be found in our cohort profile paper (Yu et al., 2020).

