The level of inflammatory biomarkers and NfL in the blood will be assessed using an ELISA assays as previously described(Cheah et al., 2017). We decided to measure pro-inflammatory cytokines because both inflammatory damage has been well documented in both AD pathophysiology and the biology of aging(Querfurth and LaFerla, 2010) and the biology of aging(Franceschi et al., 2018). NfL levels have been suggested as a blood-based biomarker for neurological diseases (Fan et al., 2023). The level in plasma increases in preclinical Alzheimer’s disease (AD) before symptoms appear (Preische et al., 2019) and correlate with MCI and other AD hallmarks, such as brain shrinkage and tau tangles observed on PET scans (Raket et al., 2020). Here, we will use plasma NfL as a systemic biomarker for cognitive decline. We will generate epigenome-wide methylation data using the state-of-the-art Illumina Infinium MethylationEPIC BeadChip (Pidsley et al., 2016) on the HiScan system. The array covers over 850,000 methylation sites per sample at single-CpG site resolution, and provides unparalleled coverage of CpG islands, RefSeq genes, ENCODE open chromatin, ENCODE transcription factor binding sites, and FANTOM5 enhancers, as well as regions identified by the ENCODE project as potential enhancers. This epigenome approach will help shed light on unknown pathways and is superior to traditional approaches that focus on a limited number of genes. We will calculate epigenetic clocks using established methods and use these clocks as a quantitative measure of biological age compared with chronological age.

Furthermore, we will measure plasma ergothioneine levels using liquid chromatography-mass spectrometry at baseline, 12 months and 24 months. Correlating changes in blood ergothioneine levels with cognitive outcomes and with pathological and aging-related biological markers will shed light on ergothioneine’s mediating role in the hypothesized relationship between mushroom consumption and cognitive aging. The inclusion of biomarkers of both a mushroom-derived compound and of aging and dementia represents a novel approach not previously adopted in human studies.

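### The methylation risk score takes its loci and weights from a single screen with no separate evaluation data; if the exposure is trial arm and the score is used in the same participants, its arm separation is inflated

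*Protocol article*

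**What the plan says.** The epigenetic paragraph of section 3.5 (Methods of analysis) opens with its purpose: "To examine the epigenetic changes associated with ET-Rich mushroom consumption". The screen is described as follows: "Single-marker tests using logistic regression will be used to examine the association of mushroom consumption with each autosomal CpG site (yes/no), adjusted for age and" (the last covariate in that sentence is sex), with control-probe principal components as further covariates. The only adjustment of the results is this: "Finally, the association results will be adjusted for the genomic control inflation factor". The score comes next: "We will subsequently develop a methylation risk score (MRS) model by taking a weighted approach (by effect size) for the CpG loci identified" as associated with mushroom consumption. No significance threshold for a locus to count as identified is given, and no separate sample or cross-fitting is mentioned.

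Two other places bear on the point. Aim 4 in section 2 is to "explore epigenome-wide DNA methylation changes following mushroom powder intervention and assess whether such changes correlate with cognitive and biomarker outcomes"; it does not name the score. Section 3.1 notes that "DNA methylation and inflammation markers have already been measured in over 600 samples from DaHA participants", but does not say that those samples will be used to derive or validate the score.

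**The concern.** A score built from sites that passed a screen, weighted by the effects estimated in that screen, carries the chance imbalances that got the sites selected. Each selected site is weighted towards the arm in which it happened to be higher. Scored in the same participants, these imbalances add up, and the score separates the arms even if the product changes no site. Genomic control does not cure this: it rescales all test statistics by one factor and removes neither the selection nor the inflation of the weights.

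Two readings of the trial would be at risk. One is a between-arm comparison of the score, presented as evidence that the product alters methylation. The other is a pooled correlation of the score with cognition. A score that is largely a proxy for arm will correlate with anything that the product changes by any route, and this could be mistaken for methylation carrying the effect.

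**Working it through.** **The plan's own figure.** The article gives no figure for the score. Its sample size can be reproduced: 2 × (1.960 + 1.282)² / 0.30² = 233.5, so 234 per arm by the normal approximation; the noncentral t gives 235 (power 0.9007, against 0.8994 at 234). With 20% attrition, 235 / 0.8 = 294, which 300 covers. The expected number at 24 months is 300 × 0.8 = 240 per arm.

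**Inputs from the article.** Sites: "The array covers over 850,000 methylation sites per sample at single-CpG site resolution" (section 3.4), taken as 850,000. Enrolment of 300 per arm, 20% attrition and d = 0.30 are from section 3.5; equal allocation is from section 3.3.

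**Assumptions, not in the article.** The exposure is trial arm; no site is truly affected; sites are independent; a two-sample comparison stands in for the covariate-adjusted logistic test. The selection threshold is unstated, so a range is shown.

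**Step 1: false loci and their smallest apparent effect.** Expected false loci = 850,000 × threshold. Smallest selected |d| = z × √(2/240).

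- 1e-5: 8.5 loci, |d| ≥ 0.403
- 1e-4: 85 loci, |d| ≥ 0.355
- Bonferroni, 0.05/850,000 = 5.9e-8: 0.05 loci, |d| ≥ 0.495

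**Step 2: in-sample separation of the score.** With weights w = d, separation = Σ(w·d)/√Σw² = √Σd², which is at least √k × the smallest |d| for k loci. At 1e-5 this floor is √8.5 × 0.403 = 1.17 SD; at 1e-4 it is √85 × 0.355 = 3.27 SD. Two separate calculations bear this out: draws of the selected z values from the null tail (300 replicates), and 15 fully simulated null trials with 850,000 sites each.

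| Selection p | Tail draws, in-sample | Full simulation, in-sample | Full simulation, derived in one half and scored in the other |
|---|---|---|---|
| 1e-6 | 0.55 SD (replicates with any locus) | not run | not run |
| 1e-5 | 1.23 SD | 1.25 SD | −0.01 SD |
| 1e-4 | 3.49 SD | 3.35 SD | 0.02 SD |
| 1e-3 | not run | 9.5 SD | 0.01 SD |

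In the full simulation all 15 in-sample comparisons gave p < 1e-19 at every threshold run. In the held-out half, p < 0.05 occurred in 0, 1 and 1 of 15 trials at 1e-5, 1e-4 and 1e-3.

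**Step 3: Bonferroni.** The chance of any false locus is 1 − (1 − 5.9e-8)^850,000 = 4.9%, so under the null the score would be empty in about 95% of trials. Any locus that does pass has an apparent |d| of at least 0.49, so its weight is prone to inflation.

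**Step 4: pooled correlation with cognition.** Correlation of score with arm = D/√(D² + 4): 0.53 at D = 1.25 and 0.86 at D = 3.35 (simulated 0.52 and 0.86). Correlation of arm with cognition at d = 0.30: 0.30/√(0.09 + 4) = 0.148. The products are 0.08 and 0.13; the simulated pooled values are 0.084 and 0.142. The two-sided 5% critical value at n = 480 is 1.96/√480 = 0.089. If the arm has no effect on cognition, the simulated pooled correlation is near 0 (0.006 at 1e-5, 0.014 at 1e-4). Within arm it is near 0 in either case (−0.003 and 0.005).

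**The case against.** The strongest reply is that the harmful use is not in the text. Section 3.5 says only that a score will be developed. It does not say that the score will be compared between arms, evaluated in the same participants or correlated with cognition, and Aim 4 speaks of methylation changes, which could be examined site by site. This stands. A reader might infer that the plan as written separates the arms by construction, or that the score cannot serve Aim 4; the article supports neither without the further step of in-sample use.

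Second, the exposure is not defined as arm. Elsewhere in section 3.5 mushroom consumption is the cohort's term, and methylation data exist for DaHA, so deriving the score in one source and applying it in the other is not excluded. This stands in part. The reference to an ET-rich product, the wording of Aim 4 and the limit on habitual mushroom intake at entry (section 3.2) make allocation the natural reading, but they do not settle it.

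Third, the size depends on an unstated threshold and on independent sites. This also stands: under Bonferroni the null problem largely vanishes, and positive correlation among selected sites would shrink the separation.

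Fourth, the missing detail could sit in a fuller document. This is only partly an answer, because the article does state where the loci and the weights come from; what it states is a single-source derivation.

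**Conclusion.** The point holds in conditional form. The article fixes a derivation in which selection, weighting and summary share one screen, with no evaluation data set apart. If the exposure is trial arm and the score is used in the participants who supplied it, its arm separation is inflated: with no true effect, about 1.2 SD at p<1e-5 and about 3.4 SD at p<1e-4, against about 0 SD out of sample. These figures assume 240 per arm and independent sites. At a Bonferroni threshold the remaining problem is inflated weights.

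The concern about cognition needs a second condition. Only if the product affects cognition by another route (d = 0.30 assumed) would a pooled correlation partly restate allocation, with r about 0.08 at 1e-5, just short of the 0.089 critical value, and 0.13 to 0.14 at 1e-4, beyond it. It would be wrong to infer that the correlation is spurious whatever the treatment effect.

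The analysis is exploratory. The primary endpoint, the sample size and the conduct of the trial are unaffected.

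**What to change.** Amend the sentence on the score in section 3.5 to say that the exposure is randomised arm, and that site selection and weights are estimated by K-fold cross-fitting, with selection repeated inside each fold, so that no participant is scored with weights from their own data. State the selection threshold. Include a term for arm in any model that relates the score to cognition or biomarkers.

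Weights taken from the DaHA samples would not be a sound substitute. DaHA is a recruitment source for the trial (section 3.2), so some trial participants' own data could enter the weights, and its exposure is habitual diet, not the trial extract.

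The cost is analysis code and a short change to the text, with no new samples. The weights will be slightly noisier, because each fold uses fewer participants, and the reported discrimination of the score will be lower.
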